#### Randomised controlled trial

The primary outcome measure is overall survival time defined as the interval between the date of randomisation and the date of death from any cause. Patients who have not died at the time of analysis will be censored at the date when they were last known to be alive. Follow up for survival will be collected on trial Case Report Forms (CRFs), by linking with NHS Digital and other health registries and annual hospital record checks.

Secondary outcome measures include:

Cost-effectiveness as measured by incremental cost per quality-adjusted life year (QALY) gained (combining EQ-5D-5L utility scores with overall survival data), and resource use data collection, including number and reasons for healthcare visits.Recurrence and distant metastasis encompassed by:
Disease free survival time defined as the interval between the date of randomisation and the date of a contributing event (either a recurrence (to include local, regional, and distant) or death from any cause and excluding any new primary cancer). Patients who are alive and disease-free at the time of analysis will be censored at the date when they were last known to be alive and disease-free.Time from treatment to first detection of recurrence defined as the interval between the completion of the patient’s definitive preliminary treatment (not including any neck dissection that might have been implemented at three months) and a recurrence of any nature (local, regional, or distant). Patients who die before a recurrence will be censored at their date of death.Details of recurrences, including location (specific details on site and whether local, regional, or distant), TNM stage at detection of recurrence and subsequent treatment for recurrence.
Quality of life assessed by the EORTC-QLQ-C30, EORTC QLQ-H&N43, and EQ-5D-5L questionnaires.Fear of cancer recurrence assessed quantitively by the FCR questionnaire and qualitatively by patient interviews.Patient experience measured by the CQC patient experience question.Patient self-efficacy and motivation will be assessed using responses from the individual self-efficacy and motivation questions.Time to receiving an urgent review appointment, as well as the number and timings of appointments requested (for patients in the intervention arm only).

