PETNECK2 will examine the effectiveness of PET-CT imaging - introduced at one year after completion of treatment – to determine patients at low risk of recurrence. We hypothesise that this PET-CT scan may identify some patients with asymptomatic recurrence (allowing earlier intervention with salvage therapies), but also those at very low risk of future recurrence. These low-risk patients would then receive a face-to-face education session along with an Information and Support (I&S) resource package, which includes information regarding symptom monitoring, and how to initiate an urgent appointment if they have any concerns or recurrence is suspected. Therefore, instead of regular scheduled follow-up appointments, patients would be in control of when they return for follow-up visits (patient-initiated follow-up).

This programme of work included development of a bespoke I&S resource package [35–37] and an initial feasibility study to optimise the education session and I&S resource package given prior to the phase III Randomised Controlled Trial (RCT), which will formally assess the efficacy and cost-effectiveness of this patient-initiated active surveillance strategy compared to the current standard of care routine scheduled clinical follow-up.

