### Patient selection

Patients who have histological or cytological confirmation of oral, oropharyngeal, nasopharyngeal, laryngeal or hypopharyngeal squamous cell carcinoma, are aged ≥ 18 years, are at least 11- to 14-months post completion of curative intent treatment by any modality (surgery, radiation or combination treatments), with no clinical symptoms or signs of loco-regional or distant metastasis and are able to provide written informed consent are eligible for randomisation into the PETNECK2 study. Patients with non-squamous cell carcinoma tumours, or those from sites other than those stated above, who are pregnant, have clinical symptoms or signs of loco-regional or distant metastasis, or are already enrolled in a head and neck cancer clinical trial where scheduled follow-up is a requirement of that protocol are not eligible. For those patients enrolled in the RCT, patient with head and neck cancer of unknown primary are also ineligible. Patients will be recruited from head and neck cancer units based in secondary and tertiary care settings.

For the RCT only, participant registration is permitted from 6-months post completion of curative intent treatment. This aims to increase potential recruitment by identifying participants early and introducing them to the trial. Randomisation can only be performed between 11- and 14-months post completion of curative intent treatment.

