### Statistical analysis plan

The median overall survival time and one year (post study entry, i.e., two-year follow-up) overall survival rate for each arm will be reported. These will be calculated using the Kaplan-Meier method of estimation and presented with confidence intervals. A stratified (for stratification factors and any other key prognostic indicators e.g., smoking status) Cox proportional hazards model will be used to determine the hazard ratio and associated confidence interval, which will be evaluated against the non-inferiority margin. Analysis populations will include intention to treat (ITT), modified intention to treat (mITT) and per protocol (PP) to confirm if conclusions are consistent across the analyses. The PP analysis population will be defined as the primary analysis in this case as it is a non-inferiority study. Numbers of patients who drop out or cross over from the intervention to control will be evaluated and used to determine their inclusion in the analysis populations. Analyses that account for treatment switching will be considered if patients in the intervention arm have comparable follow-up profiles to the control. If non-proportional hazards are observed, then models accounting for non-proportional hazards will be considered and explored.

Disease free survival and time to recurrence will be presented using Kaplan-Meier plots and analysed using a stratified Cox proportional hazards model in similar fashion to the analyses proposed for overall survival. If non-proportional hazards are observed, then relevant methods will be undertaken to evaluate the intervention effect (for example flexible parametric modelling).

Recurrence details (TNM staging, location, further treatment) will be analysed descriptively and tabulated by intervention arm. Further treatments (i.e., curative intent, palliative intent, and best supportive care) will be compared between the two arms.

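### Time to recurrence starts at end of treatment, 11-14 months before anyone can be randomised, and censors deaths: its Kaplan-Meier curve carries two small opposing biases and does not share an origin with DFS and OS (minor)

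*Protocol article*

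**What the plan says.** In the protocol article, under Trial outcomes (Randomised controlled trial), the clock for this secondary outcome starts at the end of treatment: "Time from treatment to first detection of recurrence defined as the interval between the completion of the patient’s definitive preliminary treatment". On deaths the same entry says: "Patients who die before a recurrence will be censored at their date of death". The neighbouring outcome has another origin: "Disease free survival time defined as the interval between the date of randomisation and the date of a contributing event". Overall survival also runs from randomisation.

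Under Patient selection, "Randomisation can only be performed between 11- and 14-months post completion of curative intent treatment", and eligible patients are those "with no clinical symptoms or signs of loco-regional or distant metastasis and are able to provide written informed consent".

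Under Statistical analysis plan, "Disease free survival and time to recurrence will be presented using Kaplan-Meier plots". Both are then modelled by stratified Cox regression, in the same manner as overall survival. The article mentions neither delayed entry nor a competing-risk method.

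**The concern.** Two features of the stated rule distort the plotted curve.

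- **Delayed entry.** A patient is observed only because he or she reached month 11-14 alive and clinically free of disease. A Kaplan-Meier curve of the interval from end of treatment nevertheless counts everyone as at risk from time zero. It must be flat at zero until month 11, and during months 11-14 its denominator includes patients who have not yet entered.
- **Competing death.** A patient who dies without recurrence can no longer recur. Censoring such deaths makes 1 minus Kaplan-Meier exceed the proportion who actually recur.

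At stake are the absolute recurrence percentages that readers of a surveillance trial will take from the plot, and whether recurrence can be read on the same axis as DFS, of which it is a component. The entry window also matters here because the intervention arm's PET-CT is done then, and the Background says: "We hypothesise that this PET-CT scan may identify some patients with asymptomatic recurrence". Those detections would fall largely where the stated risk set is wrong.

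**Working it through.** **The plan's own figures.** The article gives no figure for time to recurrence. Its overall survival design reproduces: HR = ln 0.89 / ln 0.94 = 1.883; events = 4 × (1.960 + 1.036)² / (ln 1.883)² = 89.6, so 90. Nothing below touches this.

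**Inputs from the article.** Entry at 11-14 months (Patient selection). Recurrence in about 40% of treated patients, 62% of it in year 1 and 82% within two years (Background). Control survival of 94% at 12 months (Sample size determination), an all-cause death hazard of -ln 0.94 = 0.062 per year, which serves as an upper bound for death without recurrence.

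**Assumptions.** Entry uniform over 11-14 months; the remaining 18% of recurrences spread over years 3-5; hazard d of death without recurrence 0.01-0.05 per year, which the article does not give. As a second scenario, a flat recurrence hazard of 0.08 per year.

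**Recurrence hazards from the Background.** Year 1: 0.40 × 0.62 = 24.8% of all treated patients. By year 2: 0.40 × 0.82 = 32.8%. Year-2 hazard = -ln(0.672/0.752) = 0.1125. Later hazard = -ln(0.600/0.672)/3 = 0.0378 per year.

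**Effect of ignoring delayed entry.** In month u between 11 and 14 only a fraction (u - 11)/3 of the counted risk set has entered. The cumulative hazard lost is therefore the hazard × 1.5 months: 0.1125 × 1.5/12 = 0.0141 (flat scenario 0.08 × 1.5/12 = 0.0100). At 24 months after treatment the true cumulative hazard since month 11 is 0.1125 × 13/12 = 0.1219:

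- with delayed entry: 1 - exp(-0.1219) = 11.47%
- as written: 1 - exp(-(0.1219 - 0.0141)) = 10.22%

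A simulation of 40,000 patients (d = 0.02) agrees: 11.49% against 10.26% at 24 months, and 14.62% against 13.44% at 36 months.

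**Effect of censoring deaths, from randomisation.** Cumulative incidence over a segment of length t with hazard r is S × r/(r + d) × (1 - exp(-(r + d)t)), where S is the proportion event-free at its start. With the Background rates, 1 minus Kaplan-Meier is 10.64% at 1 year and 13.95% at 2 years. Cumulative incidence is 10.59% to 10.38% and 13.85% to 13.46% for d = 0.01 to 0.05, an excess of 0.05-0.26 and 0.10-0.50 points. In the flat scenario the 2-year excess is 0.14-0.70 points.

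**Both together**, against cumulative incidence counted from month 11 (d = 0.01 / d = 0.05):

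| Months after treatment | Rates | As written | Cumulative incidence | Net error, points |
|---|---|---|---|---|
| 24 | Background | 10.22% | 11.41% / 11.17% | -1.19 / -0.95 |
| 36 | Background | 13.55% | 14.64% / 14.21% | -1.09 / -0.66 |
| 45 | Background | 15.96% | 16.97% / 16.31% | -1.00 / -0.35 |
| 24 | Flat 0.08 | 7.38% | 8.26% / 8.08% | -0.88 / -0.70 |
| 36 | Flat 0.08 | 14.50% | 15.20% / 14.60% | -0.70 / -0.10 |
| 45 | Flat 0.08 | 19.48% | 20.01% / 18.96% | -0.53 / +0.52 |

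**Between-arm comparison.** In simulated trials of 662 patients, the Cox hazard ratio was 0.989 as written, 0.988 with delayed entry and 0.989 from randomisation when the true value was 1.0. With a true value of 1.5 the three were 1.530, 1.531 and 1.530.

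**The case against.** The strongest reply is that little depends on this. Cox regression uses risk sets only at event times, and none occur before month 11. Randomisation balances entry times, and censoring deaths gives a valid cause-specific hazard ratio. All of that stands, and it is why the point is minor.

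Time since treatment is also a legitimate scale: the Background quotes recurrence on it, and the analysis section itself equates one year after entry with two years of follow-up. That stands too, but the scale then needs delayed entry.

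Finally, an unseen analysis plan could add delayed entry and cumulative incidence. It could, but the origin, the censoring of deaths and the Kaplan-Meier presentation are stated rules, and following them as written gives the biased curve.

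Three stronger readings are tempting, and the documents do not support them:

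- **A reader might infer that the endpoint overstates recurrence.** Only the censored deaths push that way. The pre-entry time pushes the other way and is the larger effect at 24 months after treatment.
- **A reader might infer that the long event-free lead-in distorts the treatment effect.** The hazard ratios above show that it does not.
- **A reader might infer that recurrence cannot be related to DFS and OS at all.** DFS already gives recurrence or death from randomisation. The defect is only that the recurrence curve itself has another origin.

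**Conclusion.** The point holds as a minor one about the descriptive curve of one secondary outcome. Ignoring delayed entry understates recurrence by about 1 point on the time-since-treatment scale (0.9 to 1.2 points at 24 months). Censoring deaths overstates it by under 1 point at 2 years from randomisation. The net error is an understatement at 24 months, shrinks with time, and can change sign late in follow-up if deaths without recurrence are frequent. Opposing errors are no safeguard, because their balance depends on the time point and on a death rate that is not known in advance.

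The sizes rest on uniform entry, smooth recurrence hazards and the assumed d. They do not model a cluster of PET-CT detections just after randomisation. Patients enter clinically recurrence-free, not proven recurrence-free. The cause-specific hazard ratio is essentially unaffected, and so are the primary outcome and the sample size.

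**What to change.** - Measure time to recurrence from randomisation, as for DFS and OS. If the treatment origin is kept, enter each patient into the risk set at the date of randomisation.
- Replace the Kaplan-Meier plot for this outcome with Aalen-Johansen cumulative incidence by arm, with death without recurrence as a competing event.
- Keep the stratified Cox model with deaths censored, and label its result a cause-specific hazard ratio.

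The cost is small: the dates of treatment completion, randomisation, recurrence and death are already needed for the stated outcomes. Delayed entry and the cumulative incidence plot need only analysis wording. Moving the origin also changes the outcome definition and its name in the protocol, which should be done before the outcome data are examined by arm.

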#### Randomised controlled trial’s internal pilot

An internal pilot is undertaken during the first 12-months of recruitment into the RCT. Within this, the following go/no go targets are monitored:

Recruitment: >100 subjects over the first 12 months;Drop-out rate, cross over and withdrawal rates < 15%; and.Completion of baseline patient reported outcomes > 75%.

### Statistical analysis plan

The median overall survival time and one year (post study entry, i.e., two-year follow-up) overall survival rate for each arm will be reported. These will be calculated using the Kaplan-Meier method of estimation and presented with confidence intervals. A stratified (for stratification factors and any other key prognostic indicators e.g., smoking status) Cox proportional hazards model will be used to determine the hazard ratio and associated confidence interval, which will be evaluated against the non-inferiority margin. Analysis populations will include intention to treat (ITT), modified intention to treat (mITT) and per protocol (PP) to confirm if conclusions are consistent across the analyses. The PP analysis population will be defined as the primary analysis in this case as it is a non-inferiority study. Numbers of patients who drop out or cross over from the intervention to control will be evaluated and used to determine their inclusion in the analysis populations. Analyses that account for treatment switching will be considered if patients in the intervention arm have comparable follow-up profiles to the control. If non-proportional hazards are observed, then models accounting for non-proportional hazards will be considered and explored.

Disease free survival and time to recurrence will be presented using Kaplan-Meier plots and analysed using a stratified Cox proportional hazards model in similar fashion to the analyses proposed for overall survival. If non-proportional hazards are observed, then relevant methods will be undertaken to evaluate the intervention effect (for example flexible parametric modelling).

Recurrence details (TNM staging, location, further treatment) will be analysed descriptively and tabulated by intervention arm. Further treatments (i.e., curative intent, palliative intent, and best supportive care) will be compared between the two arms.

Qualitative data from both arms of RCT will be analysed at two time points using thematic analysis [50]. This analytical method was selected as it is a flexible approach and considers both inductive and deductive approaches employing a Leventhal’s self-regulation model to guide us as a theoretical lens [51]. The self-regulation model will help understand the patients’ illness perceptions/beliefs, symptom appraisal, and how they interact with emotional experiences such as fears about cancer recurrence. We will employ this model to guide our analyses inductively. The thematic analyses will be conducted in six phases: phases one and two: familiarisation and coding; phase three: theme development; phases four and five: reviewing and refining themes; phase six: producing the report. We will aim to explore if there are any qualitative differences in the way that the intervention helps or hinders with fears of cancer recurrence and how these fears change or do not change over time.

The overall FCR score will be analysed as a continuous outcome with summary data presented to summarise scores at the baseline and 12-month timepoints. A t-test of the change from baseline to 12 months will be assessed to determine any difference between the two arms. Linear regression will also be employed to model FCR score and adjust for any important factors.

The symptom and function scores will be calculated for each of the EORTC questionnaires returned and presented graphically and compared across the assessment time points. The overall global score from the EORTC questionnaires and the EQ-5D-5L score (and thermometer) will be compared between arms and analysed using longitudinal methods with consideration being given to missing data. Differences in all measures (overall, function and symptom) will be evaluated over time using appropriate regression analysis adjusting for baseline domain scores and other key factors where applicable. EQ-5D-5L and survival will be combined to determine QALYs for the health economic analysis.

For the patients on the intervention arm, the individual self-efficacy and motivation questions will be summarised at the evaluated timepoints and also used to determine composite scores for: (i) self-efficacy and confidence; (ii) personal motivation; and (iii) external motivation factors. These will also be correlated with intervention resource usage.

For the requested appointments descriptive reporting on the data will be performed. The duration it takes patients on the intervention arm to have a visit once it has been requested will be summarised.

The frequency and timing of the appointments requested by patients on the intervention arm will be summarised. A summary of the reasons for requesting those appointments will be provided. A comparison between intervention arms for counts of follow-up visits will be undertaken using Poisson regression.

There are no formal interim analyses.

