**Fig. 2 Fig2:**
[figure not shown]
PETNECK2 randomised controlled trial schema. Schema for the PETNECK2 randomised controlled trial to assess the efficacy and cost-effectiveness of patient-initiated active surveillance compared to the routine clinical follow-up. * 6-to-14 months post-treatment is permitted for registration into the RCT. Randomisation must occur 11–14 months post-treatment. HNC, head and neck cancer; I&S, information and support; PROM, patient-reported outcome measures; RCT, randomised controlled trial

Randomisation of 698 patients is performed electronically with a 1:1 allocation ratio and remotely by recruiting centres, using a computer minimisation program incorporating a random element developed by the Cancer Research UK Clinical Trials Unit (CRCTU), Birmingham, UK. Stratification variables are: centre; HPV status/tumour site combination; tumour stage; and baseline FCR score.

Recruitment will be over 33 months, with participants followed up for at least 12 months from randomisation, incorporating follow-up using electronic medical records.

A list of the PETNECK2 centres can be requested from the PETNECK2 Trial Office ([contact]). The Standard Protocol Items: Recommendations for Intervention Trials (SPIRIT) checklist is provided as Additional File 1 [39]. The World Health Organization (WHO) Trial Registration Data Set is provided in Additional File 2.

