#### Sample size determination

The sample size for the RCT has been determined assuming a baseline control overall survival proportion of 94% at 12 months (derived from H&N5000 cohort data [52] and accounting for drop out through recurrence and death during the first year after treatment prior to entering the study). The non-inferiority margin proposed is a 5% difference in overall survival, which corresponds to a hazard ratio of 1.88. Using Jungs calculation [53] and the above design parameters, in order to detect a non-inferiority margin of 5% (i.e., lower confidence interval of intervention proportion must remain above 89%) with a one-sided alpha of 2.5% and a power of 85%, 90 events would be required, and 662 patients recruited. Inflating this number to account for 5% dropout (as observed in the completed PET-NECK [33] and De-ESCALaTE [54] trials in a comparable population) a trial sample size of 698 patients is required.

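### Read literally, the primary Cox model crosses centre with all the other stratification factors, and the unstratified 90-event, 85%-power calculation makes no allowance for the information this discards

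*Protocol article*

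**What the plan says.** Protocol article, Statistical analysis plan: the primary comparison of overall survival comes from "A stratified (for stratification factors and any other key prognostic indicators e.g., smoking status) Cox proportional hazards model". That model gives the "hazard ratio and associated confidence interval, which will be evaluated against the non-inferiority margin". The same section repeats the stratified Cox model for disease free survival and time to recurrence.

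Randomised controlled trial (RCT) section, under Fig. 2: "Randomisation of 698 patients is performed electronically with a 1:1 allocation ratio", by minimisation with a random element. "Stratification variables are: centre; HPV status/tumour site combination; tumour stage; and baseline FCR score". The number of centres is not given (a list is available on request), nor are the levels of any factor.

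Sample size determination: the calculation is made "assuming a baseline control overall survival proportion of 94% at 12 months". The margin is "a 5% difference in overall survival, which corresponds to a hazard ratio of 1.88". It concludes that, "with a one-sided alpha of 2.5% and a power of 85%, 90 events would be required, and 662 patients recruited". Allowing for 5% dropout gives 698. Stratification is not mentioned.

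Nothing in the article takes centre out of the model, pools sparse strata, or says that the factors enter as covariates.

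**The concern.** A Cox model stratified on several factors uses their full cross-classification. Each stratum has its own baseline hazard, and arms are compared only within strata. A death in a stratum where only one arm is still at risk adds nothing to the estimate. Minimisation balances the margins of the factors, not these cells, so thin cells will often hold one arm only.

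The 90 events were calculated as if every death carried full information. If centre is crossed with three or four other factors, many do not. The standard error of the log hazard ratio rises, and the upper limit may then cross 1.88 even when the two pathways have equal survival. The cost is precision: a truly non-inferior pathway could miss its margin because of the model.

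**Working it through.** **1. Reproduce the plan's figures (unstratified).**
- Margin: ln(0.89)/ln(0.94) = 1.883, stated as 1.88.
- Events: 4(1.960 + 1.036)²/(ln 1.88)² = 35.91/0.3985 = 90.1. At 1.883 it is 89.6, so 90.
- Deaths expected: monthly hazard λ = −ln(0.94)/12 = 0.005156 in both arms, with follow-up uniform on 12-45 months (33 months of accrual plus 12). Proportion dying = 1 − (0.940 − 0.793)/(33λ) = 0.1356, and 662 × 0.1356 = 89.8.
- Dropout: 662/0.95 = 697, against 698 stated (an even number).

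The plan's figures are therefore sound for an unstratified comparison.

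**2. Information under stratification.** With equal hazards, a death in a stratum where a fraction p of those at risk are in the intervention arm contributes p(1 − p). This is at most 1/4, and 0 if one arm is absent. Let R be the sum of these contributions divided by D/4, with D = 90. Then power = Φ(ln 1.88 × √(R × 90/4) − 1.96).
- R = 1: 0.6313 × √22.5 − 1.96 = 1.034, so 85%.
- R = 0.63: 0.6313 × √14.18 − 1.96 = 0.417, so 66%.
- R = 0.39: 46%.

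**3. Simulation.** 662 patients, about 90 deaths, true hazard ratio 1, Cox partial likelihood stratified on the full cross-classification, success if the upper 95% limit is below 1.88. Centres and levels are assumptions: 8 cells is 2 × 2 × 2 for HPV/site, stage and FCR; 12 is 3 × 2 × 2; 32 is 4 × 2 × 2 with two-level smoking added. The last column is the spread over repeated sets of runs.

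| Centres × cells | Strata | Patients per stratum | Deaths that contribute | R | Power, formula | Power, simulated |
|---|---|---|---|---|---|---|
| Unstratified | 1 | 662 | 90 | 1.00 | 85% | 84-87% |
| 5 × 8 | 40 | 16.6 | about 88 | 0.90 | 81% | about 80-82% |
| 10 × 12 | 120 | 5.5 | 76-77 | 0.77 | 75% | 73-78% |
| 20 × 12 | 240 | 2.8 | 62-64 | 0.63 | 66% | 63-67% |
| 30 × 12 | 360 | 1.8 | 51-56 | 0.53 | 59% | 56-63% |
| 20 × 32 | 640 | 1.0 | 36-38 | 0.39 | 46% | 41-48% |

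The sets of runs differ in replicates and in how centre sizes were drawn. With 400 replicates the Monte Carlo standard error is about 2 to 2.5 points, so single figures should not be read to the point.

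**4. Where the loss comes from.** Centre as the only stratum (10-40 centres) keeps 91-98% of the information, with simulated power about 80-85%. The other factors plus smoking, without centre (16-48 cells), keep 88-96%, with power about 79-82%. The large loss arises only when centre is crossed with the rest.

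**5. What this does to the decision.** The standard error of the log hazard ratio is 2/√(90R). The largest observed hazard ratio that still passes is 1.88 × exp(−1.96 × SE):
- unstratified (SE 0.211): 1.24
- 20 × 12 (SE 0.266): 1.12
- 20 × 32 (SE 0.338): 0.97, so the intervention arm would have to look better than control.

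**The case against.** The strongest reply is that this is one sentence in a journal article. The full analysis plan, not shown, may set the factor levels, pool sparse strata or handle centre separately. A list that runs from stratification factors to prognostic indicators such as smoking is also how covariate adjustment is often described, so *stratified* may be loose for *adjusted*. On that reading most of the loss does not arise.

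Part of this stands. The intended model cannot be settled from the article, and the size of the loss cannot be fixed without the numbers of centres and levels. The open-ended list of prognostic indicators is by itself detail that a protocol commonly leaves to the analysis plan, so it is not a fault here.

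What does not stand is that nothing has been stated. The article names a stratified model, makes its interval the decision rule, and repeats the term for two further endpoints. For FCR and quality of life it speaks instead of regression that adjusts for factors. A statistician following the text would stratify, and centre is on the list.

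A reader might infer that most strata must be uninformative, or that the trial will probably be inconclusive. The documents do not support either. With 5 centres and 8 cells, 86% of strata are informative. With 12 cells and up to 30 centres, success remains more likely than not.

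**Conclusion.** The point holds as a mismatch between the stated analysis model and the stated power. The sample size is right for an unstratified comparison. The model as literally described delivers less than 85% in every fully crossed scenario examined, from about 80-82% in the mildest shown to about 41-48% with 20 centres and 32 cells.

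The mechanism is certain. The size rests on assumed numbers of centres and levels, on *stratified* meaning full cross-classification, and on about 90 deaths with equal survival in the two arms. The per-protocol primary population could lower the number of deaths further, which is not counted here. It should be corrected before analysis because this model decides the trial and the correction is cheap.

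**What to change.** State in the statistical analysis section that centre is not crossed with the other factors in the primary Cox model. Enter HPV status/site, stage, baseline FCR and any prespecified prognostic factor such as smoking as covariates, or use a few coarse strata. Take centre as a random effect (shared frailty) or leave it out of the strata. Apply the same model to disease free survival and time to recurrence.

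If full stratification is really intended, restate the power for that model using the actual numbers of centres and factor levels. If *stratified* was meant as *adjusted*, correct the word.

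The cost is a wording change in the protocol and the analysis plan, plus a power recalculation only if full stratification is kept. With either of the wording changes, no extra patients, visits or data are needed.
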